#### Shedding analysis

2.12.4

The total shedding rate of each group and the comparison of shedding due to adverse events will be calculated using the Pearson chi-square test.

#### Statistical description

2.12.5

The measurement data will be used to calculate the mean, standard deviation, interquartile range, median, and so on. Count and rank data will be calculated for frequency and composition ratio, as well as median and average rank. Qualitative data will be given the positive rate, the number of positive, and denominator cases.

#### Analysis of baseline data

2.12.6

It includes demographic indicators, preintervention general conditions, and laboratory indicators. The measurement data will be tested by *t* test or *t*’ test (heterogeneity of variance); the count data will be assessed using Pearson chi-square test; and the rank data is tested by Wilcoxon rank sum test.

#### Compliance analysis

2.12.7

Compliance analysis will be performed according to the dose and time of administration.

#### Primary outcome

2.12.8

The 28-day all-cause mortality difference will be compared using Pearson chi-square test and logistic regression analysis with adjustment for the variables may affect mortality rate.

#### Secondary outcome

2.12.9

Quantitative variables will be compared between groups using a 2-sample *t* test. Repeated measures variables will be compared between groups using covariance analysis or mixed linear model analysis. The Pearson chi-square test will be used for qualitative variables, and the Wilcoxon rank sum test will be used for grading variables.

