### Data collection

2.7

The patients enrolled in the group will receive clinical or laboratory assessments (Table 1) during the screening period, the drug infusion period, on the first day after the end of trial interventions, and on the 28th day after enrollment. Before treatment (D0; screening period), the following indicators should be evaluated: pathogen culture results, the level of blood 5-HT, acute physiology and chronic health evaluation (APACHE II) scores, and SOFA scores. Before treatment (D0; screening period), on the third day of treatment (D2), and on the first day after treatment (D4), the following indicators will be measured: immune function indicators (white blood cell count, peripheral lymphocyte count, CD4+ and CD8+ T-cell count), renal injury indicators (Cys C), inflammation Indicators (the level of IL-6, CPR, ESR, SOD), and infection indicators (the level of serum PCT, fungi (1,3)-beta-D-Glucan, galactomannan antigen). Daily assessment indicators include the following: liver injury indicators (the level of ALT, AST, total bilirubin, direct bilirubin), the level of blood lactate, renal injury indicators (the level of Cr, BUN), lung injury indicators (oxygenation index, not applicable during extracorporeal membrane oxygenation (ECMO) support), fluid balance, vasoactive drug dose, urine volume, SOFA scores, and concomitant medications that may affect the outcome. Other indicators are the duration of organ function replacement therapy including continuous renal replacement therapy (CRRT), ECMO and mechanical ventilation, the incidence of new dysfunction, ICU stay time, ICU mortality, and 28-day mortality. Safety indicators include adverse reactions and the incidence of serious adverse events. Among them, the 28-day survival information of patients will be obtained by telephone follow-up. For dropout events, the causes will be recorded in detail and these patients will also be followed up. All the laboratory outcomes will be taken from the Central Laboratory of Zhujiang Hospital, and all the indicators needed to calculate the APACHE II score and SOFA score will also be recorded in detail. Furthermore, during the course of treatment, any out-of-plan evaluations of the above indicators by the treating physicians also will be collected. All of the above data will be collected by highly trained clinical observers.

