#### Secondary outcome

2.8.2

The secondary outcome indicators mainly include the following aspects:

Requirements for organ function support: the duration of organ function replacement therapy including CRRT, ECMO, and mechanical ventilationImprovement of organ function: the changes in SOFA score; creatinine, transaminase, and cystatin after interventions completion; lactate clearance after interventions completion; and the incidence of new organ dysfunctionImprovements in infection indicators: the changes in PCT after interventions completion, PCT clearance after interventions completion, and changes in fungi (1,3)-beta-D-Glucan and galactomannan antigen after interventions completion.Improvement of inflammatory indicators: the changes in IL-6, ESR, SOD, and CRP after interventions completionImprovement of immune function indicators: the changes in lymphocyte count, white blood cell count, and CD4+ and CD8+ T cell count after interventions completion.The incidence of new organ dysfunction: the incidence of new acute liver injury, kidney injury, and lung injury. New organ failure refers to organ failure that occurs after enrollment.Other indicators: ICU length of stay (LOS).Additionally, we will also collect blood 5-HT levels before and after completion of the treatment to determine if there is a correlation between 5-HT levels and the prognosis of sepsis.

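### Organ-support duration and ICU stay are compared by t test with no allowance for death, so if mortality differs the arm with more deaths can appear to need less support

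*Protocol article*

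**What the plan says.** **Endpoints.** Section 2.8.2 (Secondary outcome) lists how long patients receive CRRT, ECMO and mechanical ventilation, under the label of organ-support requirements. It also lists "ICU length of stay (LOS") and, under improvement of organ function, changes in "creatinine, transaminase, and cystatin after interventions completion".

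**Tests.** Section 2.12.9 (Secondary outcome) says "Quantitative variables will be compared between groups using a 2-sample" t test. It adds: "Repeated measures variables will be compared between groups using covariance analysis or mixed linear model analysis".

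**Surrounding rules.**
- Section 2.12.2 allows a transformation, and then a nonparametric method, when parametric conditions fail.
- Section 2.12.3 gives last observation carried forward as the only rule for missing data.
- Section 2.7 collects daily "renal injury indicators (the level of Cr, BUN"), and for the lung it records "oxygenation index, not applicable during extracorporeal membrane oxygenation (ECMO) support".

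No section says how a patient who dies on support or in the ICU enters the duration comparisons. No section says how creatinine measured during CRRT is treated.

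**The concern.** Death stops the ventilator, the CRRT circuit and the ICU stay. A raw count of days therefore gives an early death a low number, and in an outcome labelled as a requirement for support a low number reads as good. A patient kept alive goes on adding days.

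If granisetron saves lives, these outcomes are pushed against it. If it costs lives, they are pushed in its favour. This matters because section 2.11 expects about one third of control patients to die and powers the trial for a large difference in deaths. The article fixes both the endpoint and the test, so an analysis that follows it would carry the problem.

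Creatinine raises a separate and smaller question. CRRT removes it from the blood, so the arm with more CRRT can show lower values for the same kidney injury.

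**Working it through.** **Inputs from the documents (section 2.11).** Control mortality about 33%; difference 20%; two-sided alpha 0.05; power 80%; 15% added for losses; 77 per arm. Mortality on granisetron is then 33% − 20% = 13%. Every duration and death time below is an assumption, because the documents give none.

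**1. The plan's own figure.** With unpooled variance, n per arm = (1.960 + 0.842)² × (0.33×0.67 + 0.13×0.87) / 0.20² = 7.85 × 0.3342 / 0.04 = 65.6. Adding 15% gives 75.4 (×1.15) or 77.1 (÷0.85). The arcsine formula gives 66.4, then 76.4 or 78.1. Both agree with the stated 77. The pooled-variance formula gives 69, then 80 or 82, which is less close. A relative 20% reduction (33% to 26.4%) would need 752 per arm before losses, so the 20% must mean percentage points. No design figure is stated for the secondary outcomes.

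**2. Shift in mean raw duration.** Let m be mortality, D the mean days accrued by patients who die, and S the mean days accrued by survivors, with the drug having no effect on D or S. The arm mean is m·D + (1−m)·S. The 13% arm minus the 33% arm is 0.20 × (S − D).

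| D / S (assumed days) | 33% arm | 13% arm | Gap | Gap at 33% vs 23%, 0.10 × (S − D) |
|---|---|---|---|---|
| 4 / 10 | 8.02 | 9.22 | 1.20 | 0.6 |
| 5 / 12 | 9.69 | 11.09 | 1.40 | 0.7 |
| 6 / 14 | 11.36 | 12.96 | 1.60 | 0.8 |

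At equal mortality the gap is 0.

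**3. Simulation of the planned test.** 77 per arm, 4,000 runs. The underlying duration is the same in both arms (lognormal, mean 10 days, SD 6, capped at 28) and is cut short in patients who die, at exponential times with the mean shown.

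| Mortality | Mean death time (days) | Raw duration, higher-mortality arm minus other | t test significantly favours the higher-mortality arm |
|---|---|---|---|
| 33% vs 13% | 4 | −1.3 days | 30% |
| 33% vs 13% | 7 | −1.0 | 20% |
| 33% vs 13% | 12 | −0.7 | 14% |
| 33% vs 23% | 4 to 12 | −0.6 to −0.4 | 11% to 6% |
| 33% vs 33% | 4 to 12 | about 0 | about 2.5%, as expected by chance |

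**4. Does the nonparametric fallback help?** No. A rank-sum test on the same raw days still places early deaths among the shortest durations.

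**5. Days alive and free of support to day 28, death = 0.** Survivors with 10 days of support have 28 − 10 = 18 free days. The arm means are 0.67×18 = 12.1 and 0.87×18 = 15.7, a difference of 3.6 days against the arm with more deaths. With 12 days of support they are 0.67×16 = 10.7 and 0.87×16 = 13.9, a difference of 3.2. In the simulation the higher-mortality arm was about 3.6 days worse. A t test on free days found this in about 71% of runs at 33% vs 13%, and never in the opposite direction. At 33% vs 23% it was about 1.8 days worse, significant in about 22% to 23%. The rank-sum test on free days was not simulated.

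**6. Creatinine.** Assume levels of 100 without kidney injury, 400 with untreated injury and 150 on CRRT, with injury in 40% of both arms. If every injured patient is on CRRT, the mean is 0.6×100 + 0.4×150 = 120. If half are, it is 0.6×100 + 0.2×150 + 0.2×400 = 170. With equal baselines the change differs by the same 50, although kidney injury is identical. Neither a t test nor a mixed model removes this, and carrying the last observation forward can carry a CRRT-lowered value to the end.

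**The case against.** **Much of this rests on silence.** The article does not state that a death on day 2 scores two days, and section 2.12.1 or a fuller plan could be applied so that deaths are scored differently. This has some weight: the wrong-way scoring is what follows from comparing duration as written, not something the article asserts. But the endpoint and the test are both specified, and a t test on duration leaves no place for death.

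**The bias is conditional.** A reader might infer that these outcomes are bound to mislead. They are not. With equal mortality there is no bias, with a 10-point difference it is roughly half as large, and all day counts are assumed. Mortality is also collected alongside and would be visible.

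**The t test is a poor fit to skewed durations.** A reader might add this, but section 2.12.2 already provides for transformation or a nonparametric method.

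**Free days largely re-measure mortality.** This stands. In step 5 the underlying need is identical, so the whole signal comes from deaths. A competing-risk analysis, or durations shown beside mortality, would also be defensible. It is a reason to show the components, not to keep raw duration.

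**Creatinine is not governed by the t test.** Agreed: it is measured daily and analysed as a change, so the covariance or mixed-model sentence fits better. CRRT duration, cystatin, SOFA change and new kidney injury are also outcomes, so unequal CRRT use would not be hidden. It is also tempting to read the ECMO note as ranking such patients worst; section 2.7 only sets the oxygenation index aside.

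**Conclusion.** The point holds for CRRT, ECMO and ventilation duration and for ICU length of stay. As planned, the arm with more deaths can look as if it needs less support. At the design mortalities the spurious gap is about 0.7 to 1.6 days: 1.2 to 1.6 by direct arithmetic and 0.7 to 1.3 by simulation, all under assumed durations. The t test would significantly favour the wrong arm in 14% to 30% of simulated trials. The direction requires only that patients who die accrue fewer days than survivors and that mortality differs.

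Secondary outcomes alone are affected. Nothing here touches the 28-day mortality comparison or the 154 patients. The sponsor should correct it before unblinding.

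Creatinine is a lesser, separate point: a rule for values taken during CRRT is needed, and its size cannot be estimated from the documents.

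**What to change.** **Sections 2.8.2 and 2.12.9.** Make the compared outcomes (a) days alive and free of CRRT, ECMO and ventilation and (b) days alive and out of ICU, each to day 28, with death by day 28 counted as 0 and so ranked worst. Compare them by the Wilcoxon rank-sum test. State whether the three supports are counted separately or together. Report 28-day mortality and duration in survivors beside them, as description without a test.

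**Creatinine.** State that values taken during CRRT are not analysed at face value. One option is to treat them as not applicable, as section 2.7 does for the oxygenation index on ECMO, and to report CRRT use by arm alongside. The same applies to BUN if it is reported; it is collected but not named in section 2.8.2.

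**Cost.** Mainly wording and programming. Two cautions apply. The composite mixes death with duration, so its components must always be shown. Section 2.7 lists support durations, ICU stay and 28-day survival by telephone, but does not show that support or ICU status is followed to day 28 after a first ICU discharge, including readmission. That must be confirmed or added to the case report form.

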### Sample size

2.11

According to previous clinical experience, the mortality rate of sepsis in this study center is about 33%. Our sample size was calculated to detect a 20% difference in mortality on day 28 between the 2 groups with a 2-tailed test, a = 0.05, β = 0.2 (power = 80%). Considering some factors such as shedding and loss of follow-up, an additional 15% of the sample size was added, resulting in a total of 154 patients, 77 in the control group, and 77 in the treatment group.

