#### Survival analysis

2.12.10

If the 60-day survival information of patients is obtained, the time of death in the 60-day survival of the 2 groups of patients will be described as Kaplan–Meier plots, and survival differences will be tested using the Cox proportional hazard model.

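### New liver, kidney and lung injury are tested only by an unadjusted chi-square although APACHE II and SOFA are collected before treatment: a valid test that gives away some power

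*Protocol article*

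**What the plan says.** All references are to the protocol article.

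- **2.8.2 Secondary outcome** lists the incidence of new acute liver, kidney and lung injury, counted from enrolment. Each is a yes/no outcome.
- **2.12.9 Secondary outcome** fixes the test for such variables: "The Pearson chi-square test will be used for qualitative variables". Covariance analysis and the mixed linear model are named in the same section, but only for repeated measures. They do not reach a yes/no incidence.
- **2.7 Data collection** schedules "acute physiology and chronic health evaluation (APACHE II) scores, and SOFA scores" before treatment (D0) and says that the components of both scores are recorded.
- **2.12.8 Primary outcome** gives 28-day mortality a chi-square and also "logistic regression analysis with adjustment for the variables may affect mortality rate".
- **2.12.11 Subgroup analysis** uses APACHE II, age and multiple organ dysfunction as factors thought to influence outcome.
- **2.12.10 Survival analysis** says that "survival differences will be tested using the Cox proportional hazard model". It neither lists nor rules out covariates, and it applies only if 60-day data are obtained.

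**The concern.** The plan adjusts mortality for prognostic variables but sends the new-organ-injury outcomes to a test that cannot be adjusted. This is a stated choice of method and not a detail left for later, since no covariate list elsewhere can be attached to a Pearson chi-square.

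The outcomes matter to the trial. The introduction and discussion rest the case for granisetron largely on liver and lung protection. Entry requires organ dysfunction but sets no upper limit of severity (2.2), and 2.4 describes 1:1 allocation in blocks without mentioning stratification by severity. If baseline severity predicts new organ injury, its variation between patients stays in the crude comparison as noise that a model could remove.

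At stake is some power on secondary outcomes. The sample size was set on mortality and is not affected.

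**Working it through.** **1. The plan's own figure.** 2.11 gives a control mortality ("the mortality rate of sepsis in this study center is about 33" per cent), aims to "detect a 20% difference in mortality on day 28 between the 2 groups", uses two-sided alpha 0.05 and 80% power, and states that "an additional 15% of the sample size was added". Reading the difference as absolute (33% vs 13%), with unpooled variance:

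n = (1.96 + 0.8416)² × (0.33×0.67 + 0.13×0.87) / 0.20² = 7.849 × 0.3342 / 0.04 = 65.6 per arm; 65.6 / 0.85 = 77.1.

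The arcsine formula gives 66.4, rounded up to 67, and 67 × 1.15 = 77.05. Both agree with 77 per arm, 154 in total. A relative 20% reduction (33% to 26.4%) would need 752 per arm before dropout, so the absolute reading is the one intended.

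**2. Crude power at 77 per arm.** The article gives no rate for new organ injury, so the rates are assumed. With p̄ the mean rate and d the difference:

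power = Φ{ [d − 1.96 √(2p̄(1−p̄)/77)] / √[(p₁(1−p₁) + p₂(1−p₂))/77] }

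- 30% vs 15%: (0.15 − 1.96×0.0673)/0.0662 = 0.273, power 61%.
- 40% vs 25%: (0.15 − 1.96×0.0755)/0.0745 = 0.027, power 51%.
- 12% vs 5%: (0.07 − 1.96×0.0449)/0.0446 = −0.406, power 34%.

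The simulated crude powers agree: 61-63%, 50-52% and 35-37%.

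**3. Adjusted power.** This was simulated with logit P(event) = a(arm) + b·x, where x is a standard-normal baseline severity score and a(arm) is solved to keep the marginal rates. The crude test is the uncorrected chi-square. The adjusted test is the likelihood-ratio test for arm with x in the model. The strength b is assumed, because the article gives none.

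| Log-odds per SD (b) | Gain in power, 77 per arm, one score, across the three pairs of rates |
|---|---|
| 0 to 0.3 | about 0-1 point |
| 0.6 | 2-3 points |
| 1.0 | 3-9 points |
| 1.4 | 6-13 points |

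Single settings:

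- 30% vs 15%: crude 61-63%; adjusted 65%, 69% and 72% at b = 0.6, 1.0 and 1.4.
- 40% vs 25%: 52.0% to 56.8% at b = 0.8 (AUC 0.70); 49.9% to 60.1% at b = 1.2 (AUC 0.77).
- 33% vs 13% (the mortality rates, as a stand-in): 86.1% to 86.1% at b = 0; 85.3% to 87.6% at 0.6; 85.9% to 90.2% at 1.0.
- 12% vs 5%, two covariates, b from 0 to 1.0: 35-37% to 36-39%. Here 77×0.12 + 77×0.05 = 9.2 + 3.9, about 13 events in the whole trial.

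For scale: at 33% vs 13%, going from 67 to 77 per arm moves the crude power from 79.2% to 84.6%, 5.4 points. At 67 per arm, adjusting with b = 1.0 moves it from 81.2% to 86.3%, 5.1 points. A fairly strong score is then worth about ten patients per arm.

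**4. Type I error.** At 33% in both arms and b = 1.0, the crude test rejects 4.8% and the adjusted test 4.9%. Over all null settings tried, the adjusted test rejects 4.5-6.3% and the crude test 4.3-5.5%. With 3,000 null runs the simulation error is √(0.05×0.95/3000) = 0.4 points. With an 8% event rate and two covariates, the adjusted test rejects about 6.0% against 5.2-5.4% crude. A useless second covariate cost no power.

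**The case against.** **The chi-square is a valid test in a randomised trial.** This stands. Chance imbalance in severity is part of the sampling variation that the 5% level already covers, and nothing in 2.12.9 is stated wrongly. A reader might infer that the crude comparison is biased or that the trial's stated power is affected. The documents support neither.

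**Severity may predict new injury poorly.** This also stands. An organ that has already failed at D0 may not be able to have a new event, so the relation could be weak or non-monotone, and experience with mortality need not carry over. The range must therefore include a gain near zero.

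**The gain shrinks when events are few, and the adjusted test may then be slightly liberal.** This stands, and part of a small apparent gain can be inflated size.

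**The organ markers are not all secured at baseline.** Largely right. 2.7 puts cystatin C in the pre-treatment set, but creatinine, transaminases, bilirubin and oxygenation index among the daily assessments. That creatinine, bilirubin and oxygenation index are held at D0 follows only indirectly from the D0 SOFA score, and oxygenation index does not apply during ECMO.

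**Survival.** A reader might extend the point to 2.12.10 and say that survival is also compared unadjusted. The documents do not support this. A Cox model can carry covariates, the section excludes none, and a covariate list may properly sit in an analysis plan that is not shown. The analysis is also conditional on 60-day data, and 28-day mortality has an adjusted model.

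The objections do not remove the stated choice, for outcomes central to the rationale, of a test that cannot use severity scores the trial already collects.

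**Conclusion.** The point holds for the yes/no new-organ-injury outcomes only, as avoidable loss of efficiency. With 77 per arm and one baseline severity score, the gain runs from about 0-1 point of power for a weak predictor to about 6-13 points for a strong one (log-odds 1.4 per SD), and is smallest for rare outcomes. The direction does not depend on the assumptions beyond the score having some prognostic value. The size rests wholly on assumed event rates and assumed prognostic strength, because the article gives neither. The sample size and the primary analysis are untouched, and no claim is made about the survival analysis.

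**What to change.** In 2.12.9, for new acute liver, kidney and lung injury:

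- Make the main analysis a logistic regression on arm and continuous D0 APACHE II (or SOFA, with one of the two named in advance).
- Add that organ's own D0 marker only where it is available and event counts allow.
- Report a standardised risk difference with 95% CI, because the adjusted odds ratio is conditional on severity and is not directly comparable with the crude one.
- Keep the Pearson chi-square as a supporting analysis.
- Where events are few, keep to one covariate or name a small-sample method, because the likelihood-ratio test can then reject about 6% against a nominal 5%.

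The cost is a change of wording before unblinding. APACHE II and SOFA are already scheduled at D0, so no new data or patients are needed. Naming the covariate in advance also prevents a choice made after the results are seen.

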#### Survival analysis

2.12.10

If the 60-day survival information of patients is obtained, the time of death in the 60-day survival of the 2 groups of patients will be described as Kaplan–Meier plots, and survival differences will be tested using the Cox proportional hazard model.

